# INFORMED CONSENT

The subjects (or legal representatives of the subject) should sign the informed consent form on the first visit after fully understand of the purpose and procedure of the study. The patients should be aware that they should return for follow up visits every 3 months for one year for physical and laboratory evaluations.

# MANAGEMENT REQUIREMENTS

## Data collection

The study will be conducted in accordance with ICH guidelines and GCP standard. Investigators will first collect all original patient information by using a “Medical Record Worksheet”, which will be served as “source information” and will be kept and maintained by the investigators. As a second step, the investigators will report all data specified by the protocol onto a web-based electronic CRFs by using an EDC system (VitalEDC, VitalStrategic). Data query report will be generated automatically in real time.

A web-based study center will be designed to provide investigators with 24/7 support for the conduct of the study, which will provide an online access to study materials, training module, patient enrollment updates, study newsletter, and relevant literature (e.g. key international literature, trend and dynamics in the outcomes research area, etc.).

## Quality Control

Data quality control will include the following steps:

- EDC edit check and logic check at data entry
- Real time data query reporting and resolution;
- 100% on site monitoring ensuring adequate patient enrollment and consent, proper completetion and documentation of original medical chart, and protocol compliance
- 50% remote source document verification (rSDV) and 10% on-site SDV at each site;

Frequent data query from a specific site will trigger a data audit visit at the site. Randomly selected site auditing will also be performed to ensure proper study conduct.

Lab certification at each site will be obtained prior to enrolling patients.

## Study Duration

The study will be composed of the follow four stages:

1. Study preparation – This includes study material development (CRF, EDC, ICF, etc), site selection and qualification, and EC/IRB approval. The estimated duration is 3 months.
2. Patient enrollment – This period extends from the first to the last patient enrollment (FPI to LPI). The estimated duration is 6 months.
3. Follow up period – This period is 12 months according to the study design.
4. Data Cleaning, analysis and reporting – This period is from the completion of eCRF for all patients to the Clinical Study Report and is estimated to be 3 months.

The total duration of the study is thus estimated to be 24 months (from commencement to CSR).

## Study Structure

The study sponsor is Bristol-Myers Squibb.

The principal investigator of this study is [name], Co-chairman of CCMR Advisory Board, Director of Endocrinology Department, People’s Hospital of Peking University.

The overall scientific advisory board is the CCMR International Advisory Board [Appendix I – CCMR Execution Plan].

The Study Steering Committee will be composed of national and regional level medical experts recommended by the CCMR Advisory Board.

Study Management will be provided by VitalStrategic Research Institute, the co-organizer of the CCMR.

# ADVERSE EVENT REPORTING

## Investigators’ responsibilities

Investigators must report any Adverse Events arising out of or in connection with the Study to the Regulatory Authority in accordance with applicable laws and regulations; Investigators must report to BMS any Serious Adverse/Adverse Events relating to BMS products within 1 business day of becoming aware. Reports must be made using the CIOMS form and be sent via email to [[contact]] or [contact]). The AE handling schedule is as shown in Table 2 below.

## Definitions of adverse events

**Adverse Event (AE)** is any untoward medical occurrence in a patient or clinical investigation subject administered a pharmaceutical product and which does not necessarily have to have a causal relationship with this treatment.

Therefore, an adverse event can therefore be any unfavourable and unintended sign (including an abnormal laboratory finding, for example), symptom, or disease temporally associated with the use of a medicinal product, whether or not considered related to the medicinal product.

**Serious criteria,** one of the following reactions caused by using the medical product:

1. Results in death;
2. Is life-threatening;
3. Requires inpatient hospitalization or causes prolongation of existing hospitalization;
4. Results in persistent or significant disability/incapacity;
5. Is a congenital anomaly/birth defect;
6. Is an important medical event (defined as a medical event(s) that may not be immediately life-threatening or result in death or hospitalization but, based upon appropriate medical and scientific judgment, may jeopardize the patient/subject or may require intervention (e.g. medical, surgical) to prevent one of the other serious outcomes listed in the definition above.)

Adverse Event Reporting

| **Drugs** | **Description of report** | **Timeframe (calendar day)** | **Transmission** |
| --- | --- | --- | --- |
| Imported drugs within 5 years of first approved in China  (For example Onglyza) | Death | Immediately | Fill out the “Drug Adverse Reaction/Event Report Form”   - **Online** report: [www.adr.gov.cn](http://www.adr.gov.cn)   <Note^[[1]](#footnote-0)^>  Or   - Fax/Email: XXXXXXXX (*ADR Canter where the hospital located)*   <Note^[[2]](#footnote-1)^> |
|  | Serious or unexpected ADR | Within 15 days |  |
|  | Other ADRs | Within 30 days |  |
| Drugs beyond observation period/ imported drugs beyond 5 years of first approved in China  (For example Glucophage, Monopril) | Death | Immediately |  |
|  | Serious or unexpected ADR | within 15 days |  |

IMPORTANT:

1. Death cases shall be reported immediately.
2. Follow-up visits, if any, shall be reported promptly.

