## Secondary Objectives:

1. To evaluate the reasons and the process of each step of the changes in treatment regimen during the 12-month follow up.
2. To evaluate the influential factors related to the changes of the treatment patterns for newly diagnosed T2D, including clinical outcomes, pattern of blood glucose monitoring, social-economical status (i.e. insurance status, income status, education background, etc), patients’ compliances, patients’ knowledge of diabetes, hospital tier, specialties of the physicians;
3. To assess the incidence of CVD risk factors (i.e. hypertension, lipidemia and obesity) and the intervention patterns;
4. To assess the associated incidence of diabetic complications, including cardiovascular / cerebrovascular and microvascular diseases;
5. To assess the application of diabetes related clinical examinations such as Fundus examination and diabetic foot screening;
6. To assess the methods of diagnosis (i.e. routine physical examination, health screening, seeking health care due toT2D symptoms, seeing doctors for other diseases, etc), and location of diagnosis (i.e. the tier of hospital, the physician specialty, etc) and the influential factors.
7. To assess the incidence of hypoglycemia and other AEs and SAE, that may be related to anti-diabetes medications.
8. To access the medical resource consumption pattern for treating diabetes.
9. To evaluate the health conditions and quality of life at the baseline and at the 12th month.

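### Section 10.2 makes causation part of the definition of seriousness, contradicting its own AE definition and leaving possibly related serious events, which objective 7 asks for, outside the SAE class

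*Protocol*

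**What the plan says.** Protocol Section 10.2 (Definitions of adverse events) opens with an AE definition that sets no causal condition. The event is one "which does not necessarily have to have a causal relationship with this treatment", and the following sentence extends this to any unfavourable sign, symptom or disease "whether or not considered related to the medicinal product". The next paragraph lists six serious outcomes (death, threat to life, hospitalisation, disability, congenital anomaly, important medical event) under the lead-in "one of the following reactions caused by using the medical product".

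Secondary objective 7 (Section 3.2, repeated in the Synopsis) reads: "To assess the incidence of hypoglycemia and other AEs and SAE, that may be related to anti-diabetes medications".

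The reporting table in Section 10.2 has a row for death, a row for "Serious or unexpected ADR" with a 15-day limit and, for recently approved imported drugs only, a row for other ADRs with a 30-day limit. A note below it states "Death cases shall be reported immediately". Section 10.1 adds: "Investigators must report any Adverse Events arising out of or in connection with the Study to the Regulatory Authority".

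**The concern.** Seriousness describes what happened to the patient. Causality is a separate judgement about why. The lead-in in Section 10.2 merges them, so an AE that puts a patient in hospital is serious only if the drug is held to have caused it. That conflicts with the AE definition directly above it, and it sets a stricter test than objective 7.

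At stake is the SAE part of objective 7. The study plans about 80 hospitals in three tiers, with physicians of different specialties. If membership of the SAE class depends on each physician's causal judgement, SAE incidences may differ between sites or drugs because attribution habits differ, not because event rates do. A later analysis could not reliably repair this, since the classification is made at the site during follow-up.

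**Working it through.** No arithmetic applies. The protocol states no SAE count, rate or threshold that the definition feeds into. The check sets the passages side by side.

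**Step 1: is there another definition of seriousness?** Section 5.2 speaks of severe adverse events and Section 10.1 of serious adverse events, but neither defines the term. The lead-in in Section 10.2 is the only definition.

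**Step 2: classify one non-fatal event, a hospitalisation during drug treatment, under three causality judgements.**

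| Judgement | AE (10.2)? | Serious (10.2 as written)? | Within objective 7? |
| --- | --- | --- | --- |
| Caused by the drug | Yes | Yes | Yes |
| Possibly related or uncertain | Yes | No | Yes |
| Clearly unrelated | Yes | No | No |

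The definition and the objective disagree only in the middle row. That group is the one under-classified for objective 7. The bottom row conflicts with the AE definition, but it costs objective 7 nothing.

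**Step 3: follow the middle row into the reporting table.** The protocol does not define ADR. Assume it means a suspected reaction, and take an expected reaction that leads to hospitalisation and is suspected but not judged to be caused by the drug. As written it is neither serious nor unexpected. For a recently approved imported drug it moves from the 15-day row to the 30-day row for other ADRs. For an older drug the table has no such row, so the event falls in none. If ADR instead means a reaction already judged to be caused, the event is in no ADR row under either definition, and this consequence disappears.

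**Step 4: check what does not depend on the definition.**
- Deaths have their own row, and the note on them has no causal condition.
- Section 10.1 ties reports to the regulator to a connection with the study, not to seriousness. It gives serious and non-serious events relating to the funder's products the same deadline of one business day.
- Section 5.2 records hospitalisations with cause and outcome. The flow chart in Section 5.3 records cardiovascular events during follow-up. Secondary endpoint 5 (Section 6.2) counts cardiovascular events and stroke at 3, 6, 9 and 12 months. None of these applies a causality test.

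**Step 5: size.** Let P be the number of serious-outcome events that may be related and C the number judged to be caused. The share lost to objective 7 is 1 − C/P. The documents give neither P nor C.

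**The case against.** The strongest reply is that little depends on this label. The study observes routine care, the primary endpoint is HbA1c, and none of the ten secondary endpoints in Section 6.2 is SAE incidence (hypoglycaemia is the only safety event tied to treatment). Step 4 shows that most reporting and recording continues whatever the definition says. This stands, and it limits the severity. It does not remove the contradiction, because objective 7 names SAEs explicitly and no other passage says which events those are.

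It could also be said that "The study will be conducted in accordance with ICH guidelines and GCP standard" (Section 9.1) will lead sites to a definition based on outcome alone. The protocol does not reproduce that definition, however, and it prints a different one of its own. A site has no stated basis for preferring the unprinted text.

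Three stronger readings are tempting and are not supported:

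- **A reader might infer that unrelated deaths go unreported.** They may fall outside the serious class, but the instruction to report deaths at once is unqualified.
- **A reader might infer that a cardiovascular signal on a newer drug would be filtered out at the site.** Cardiovascular events, stroke, hospitalisations and medication are all recorded during follow-up without a causality test, so such events can be tabulated by drug without the SAE label.
- **A reader might put a large percentage on the loss.** For example, assume that 5%–15% of 5,000 patients are hospitalised or die (250–750 events) and that 2%–10% of these are called drug-caused (5–75 events). The implied loss of 90%–98% is only the complement of the assumed 2%–10%. Its base is all-cause events, most of which could lie outside objective 7. It also ignores Section 5.2, which restricts collection of severe adverse events to the funder's products.

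**Conclusion.** The point holds as an internal contradiction with a limited consequence. The causal lead-in in Section 10.2 cannot be reconciled with the AE definition above it, and it is narrower than objective 7. Serious events of possible or uncertain relation would be under-classified, to a degree that depends on the individual physician. If ADR is read as a suspected reaction, some could also be placed in the wrong reporting row or in none. The under-classification follows from the text alone; the row effect rests on that reading of an undefined term. The size cannot be derived from the documents. Severity is moderate: a stated secondary objective is affected, while the primary endpoint, the instruction on deaths and the recording of cardiovascular events and hospitalisations are not.

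**What to change.** In Section 10.2, replace the lead-in with a sentence to this effect: *a serious adverse event is any AE as defined above, regardless of causality, that meets one of the following six criteria.* Then:

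- Add a separate eCRF field for the investigator's causality judgement (related, possibly related, unrelated).
- State that a serious ADR is the subset of SAEs with suspected causality, so that the table's timetable stays as it is.
- For objective 7, report the SAEs judged related or possibly related.

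The cost is one sentence of definition, one line on serious ADRs and one eCRF field. The downside is somewhat more event classification by sites. The change does not lift the Section 5.2 restriction of severe-event collection to the funder's products. That restriction is a separate matter and must also be reconciled with objective 7 if SAE incidence is to cover all anti-diabetes medications.

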# PUBLICATION OF THE RESULTS

All the documents and data related to this study are shared with the CCMR advisory board and the study funder. All publications must be reviewed by the Steering Committee, the study sponsor, the study funder, and produced based on the publication plan. Individual investigators or institutions must obtain the written endorsement from the Steering Committee before they publish any data related to this study.

# COMPLIANCE

No patient private information that is not relevant in accordance to the protocol will be collected for this study. Patients’ identity will be kept anonymized. Investigators will ensure to collect and handle all patient data according to GCP/ICH guidelines, local laws and regulations. All data collected are true, clear and legible. No further manipulation of the data will be conducted and any means that may breach the integrity of data will be prohibited. All data collected are adequate, accurate and according to the study protocol.

The researchers will inform the subject about data collection before the start of the study. The investigator will make awareness of the subject that the data collected in this study can be transferred to the organization or institution in other countries.

Appropriate technical means and management procedures should be adopted to prevent the personal information of the subjects from being accessed or opened to the unauthorized personnel and organizations. No accidental and unlawful damage to the data and accidental loss and change of the data will occur. In the whole study period, the researchers who have the right to look over the personal information of the subjects should keep all information confidential.

# ETHICAL REVIEW

According to the national and local regulations, all the study documents should be filed, formatted and submit to the Ethics Committee (EC) or Institutional Review Board (IRB) for review and approval. No patient medical record can be accessed prior to obtaining an approval from the EC/IRB or other designated authority.

**Supplemental eChecklist**

**STROBE Statement—checklist of items that should be included in reports of observational studies**

|  | Item No. | Recommendation | Page  No. | Relevant text from manuscript |
| --- | --- | --- | --- | --- |
| **Title and abstract** | 1 | (*a*) Indicate the study’s design with a commonly used term in the title or the abstract | 1,2 | Title |
|  |  | (*b*) Provide in the abstract an informative and balanced summary of what was done and what was found | 3 | Abstract |
| Introduction | | | |  |
| Background/rationale | 2 | Explain the scientific background and rationale for the investigation being reported | 4 | Introduction |
| Objectives | 3 | State specific objectives, including any prespecified hypotheses | 4 | Introduction |
| Methods | | | |  |
| Study design | 4 | Present key elements of study design early in the paper | 5 | Methods (Study design and Population) |
| Setting | 5 | Describe the setting, locations, and relevant dates, including periods of recruitment, exposure, follow-up, and data collection | 5,6 | Methods (Study design and Population, Study procedures and Data collection) |
| Participants | 6 | (*a*) *Cohort study*—Give the eligibility criteria, and the sources and methods of selection of participants. Describe methods of follow-up  *Case-control study*—Give the eligibility criteria, and the sources and methods of case ascertainment and control selection. Give the rationale for the choice of cases and controls  *Cross-sectional study*—Give the eligibility criteria, and the sources and methods of selection of participants | 5 | Methods (Study design and Population) |
|  |  | (*b*) *Cohort study*—For matched studies, give matching criteria and number of exposed and unexposed  *Case-control study*—For matched studies, give matching criteria and the number of controls per case |  | Not applicable |
| Variables | 7 | Clearly define all outcomes, exposures, predictors, potential confounders, and effect modifiers. Give diagnostic criteria, if applicable | 6,7 | Methods, Supplemental e Protocol |
| Data sources/ measurement | 8* | For each variable of interest, give sources of data and details of methods of assessment (measurement). Describe comparability of assessment methods if there is more than one group | 6 | Methods, Supplemental e Protocol |
| Bias | 9 | Describe any efforts to address potential sources of bias | 6,7 | Methods, Supplemental e Protocol |
| Study size | 10 | Explain how the study size was arrived at | 7 | Methods, Supplemental e Protocol |

Continued on next page

| Quantitative variables | 11 | Explain how quantitative variables were handled in the analyses. If applicable, describe which groupings were chosen and why | 6,7 | Methods, Supplemental e Protocol |
| --- | --- | --- | --- | --- |
| Statistical methods | 12 | (*a*) Describe all statistical methods, including those used to control for confounding | 7 | Methods, Supplemental e Protocol |
|  |  | (*b*) Describe any methods used to examine subgroups and interactions | 7 | Methods, Supplemental e Protocol |
|  |  | (*c*) Explain how missing data were addressed | 7 | Methods, Supplemental e Protocol |
|  |  | (*d*) *Cohort study*—If applicable, explain how loss to follow-up was addressed  *Case-control study*—If applicable, explain how matching of cases and controls was addressed  *Cross-sectional study*—If applicable, describe analytical methods taking account of sampling strategy | 7 | Methods, Supplemental e Protocol |
|  |  | (*e*) Describe any sensitivity analyses | 7 | Methods, Supplemental e Protocol |
| Results | | | | |
| Participants | 13* | (a) Report numbers of individuals at each stage of study—eg numbers potentially eligible, examined for eligibility, confirmed eligible, included in the study, completing follow-up, and analysed | 7,8 | Results, Table 1 and Table 2 |
|  |  | (b) Give reasons for non-participation at each stage | 7,8 | Results, Table 1 and Table 2 |
|  |  | (c) Consider use of a flow diagram | 7,8 | Results, Table 1 and Table 2 |
| Descriptive data | 14* | (a) Give characteristics of study participants (eg demographic, clinical, social) and information on exposures and potential confounders | 7,8 | Results, Table 1 and Table 2, Supplemental Table S1 |
|  |  | (b) Indicate number of participants with missing data for each variable of interest | 7,8 | Results, Table 1 and Table 2 |
|  |  | (c) *Cohort study*—Summarise follow-up time (eg, average and total amount) | 7,8 | Results, Table 1 and Table 2 |
| Outcome data | 15* | *Cohort study*—Report numbers of outcome events or summary measures over time | 7,8 | Results, Table 1 and Table 2 |
|  |  | *Case-control study—*Report numbers in each exposure category, or summary measures of exposure |  | Not applicable |
|  |  | *Cross-sectional study—*Report numbers of outcome events or summary measures |  | Not applicable |
| Main results | 16 | (*a*) Give unadjusted estimates and, if applicable, confounder-adjusted estimates and their precision (eg, 95% confidence interval). Make clear which confounders were adjusted for and why they were included | 7-11 | Results, Table 1, Table 2, and Table 3, Figure 1 |
|  |  | (*b*) Report category boundaries when continuous variables were categorized | 7-11 | Results, Table 1, Table 2, and Table 3, Figure 1 |
|  |  | (*c*) If relevant, consider translating estimates of relative risk into absolute risk for a meaningful time period |  | Not applicable |

Continued on next page

| Other analyses | 17 | Report other analyses done—eg analyses of subgroups and interactions, and sensitivity analyses | 10,11 | Results, Table 2, and Table 3 |
| --- | --- | --- | --- | --- |
| Discussion | | | | |
| Key results | 18 | Summarise key results with reference to study objectives | 12 | Discussion |
| Limitations | 19 | Discuss limitations of the study, taking into account sources of potential bias or imprecision. Discuss both direction and magnitude of any potential bias | 16 | Discussion |
| Interpretation | 20 | Give a cautious overall interpretation of results considering objectives, limitations, multiplicity of analyses, results from similar studies, and other relevant evidence | 12-16 | Discussion |
| Generalisability | 21 | Discuss the generalisability (external validity) of the study results | 16 | Discussion and Conclusion |
| Other information | |  | | |
| Funding | 22 | Give the source of funding and the role of the funders for the present study and, if applicable, for the original study on which the present article is based | 17 | Acknowledgement |

*Give information separately for cases and controls in case-control studies and, if applicable, for exposed and unexposed groups in cohort and cross-sectional studies.

**Note:** An Explanation and Elaboration article discusses each checklist item and gives methodological background and published examples of transparent reporting. The STROBE checklist is best used in conjunction with this article (freely available on the Web sites of PLoS Medicine at http://www.plosmedicine.org/, Annals of Internal Medicine at http://www.annals.org/, and Epidemiology at http://www.epidem.com/). Information on the STROBE Initiative is available at www.strobe-statement.org.

1. [↑](#footnote-ref-0)
2. [↑](#footnote-ref-1)
